**Fig. 4 Fig4:**
[figure not shown]
**A** YBT previous direction. **B** YBT postero-medial direction. **C** YBT postero-lateral direction

Participants will perform 3 familiarizations, followed by 3 tests for each direction. The test will be invalidated if hands do not remain at the waist area, if the position of support is not maintained, if the heel does not remain in contact with the platform during reach, if volunteer unloads body weight onto the contralateral limb, or if the participant loses balance during the test [25].

For kinetic analysis during YBT execution, data will be filtered using Butterworth 2nd order 2.5 Hz low-pass filter applied in direct and reverse direction. Variables will be calculated: average speed (cm/s); anteroposterior peak speed (Y) (cm/s); mid-lateral peak speed (X) (cm/s); anteroposterior displacement amplitude (Y) (cm); mid-lateral displacement amplitude (X) (cm); average displacement (XY) (cm); and reliable ellipse area (cm^2^) [26] for each test displacement direction.

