##### Postural Control

Postural control will be evaluated during the execution of YBT using the force platform.

Postural oscillation will be evaluated through analysis of the center of pressure (CoP) displacement with data obtained during the execution of YBT, performed during use of force platform (EMGSystem do Brasil® São José dos Campos, SP), with sampling frequency being 500 Hz. Force signals obtained (Fx, Fy, and Fz) and the moments of these forces (Mx, My and Mz), will be used to determine CoP oscillation, with the direction of CoP oscillation being considered, [+x]- anterior; [+y]- right and [+z]- upper directions will also be used.

Collecting environment will have controlled temperature and noise level minimizing interference in postural control. Participants will be previously oriented as to positions that should be performed during data collection. The volunteer must be initially positioned with face facing the posterior direction of platform (−Fy).

During the execution of YBT, the volunteer will be tested in *unipodal* support under the force platform. Participants will be positioned with their foot to be evaluated at intersections of lines, formed by previous, posterior-medial, and posterior-lateral directions marked on the force platform. Participants will be verbally instructed to perform maximum reaches in three directions, with contralateral limbs, with upper limbs positioned at waist level [25] (Fig. 4).

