##### Functional performance

The execution of YBT, carried out as described above, will also be computed for each direction, anterior, postero-medial, and postero-lateral, displacement, in centimeters, performed with contralateral limb to supporting member [25] (Fig. 4). Average displacement (AD) in each direction will be normalized using the length of support leg (LS) of the individual [25], and composite score (CS) will be calculated.

CS = AD (ant + postero-medial + postero-lateral)/3 × LS (×100)

To evaluate functional performance of THT, a demarcation will be carried out, consisting of a line 6 m long and 15 cm wide, perpendicular to a starting point [27].

This test is used to measure the combination of muscle strength, neuromuscular control, and ability to tolerate sports-related activities [28]. The participant must perform 3 maximum jumps with the same leg following the trajectory of the marked line. Subsequently, the distance between starting line and the tip of Hálux at the site of the last landing must be measured in centimeters [27] (Fig. 5). Three (3) repetitions will be carried out for the member to be tested, and the best result will be computed for later analysis.

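### Two secondary-outcome derivation rules need correcting: the CoP axis labels contradict each other, and the Y-balance composite is printed without the brackets that its stated normalisation needs

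*Protocol article*

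**What the plan says.** **CoP axes.** The *Postural Control* section sets the direction of CoP oscillation with +"x]- anterior; [+y]- right and [+z]- upper directions will also be used". That makes x the anteroposterior axis and y the mediolateral axis. The same section starts the volunteer with the "face facing the posterior direction of platform (−Fy"), which treats y as the front-to-back axis. The list of derived variables, in the text after Fig. 4, has "anteroposterior peak speed (Y) (cm/s); mid-lateral peak speed (X) (cm/s") and "anteroposterior displacement amplitude (Y) (cm); mid-lateral displacement amplitude (X) (cm"), so there Y is anteroposterior and X is mediolateral. Every variable on the list is calculated for each of the three reach directions.

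**Y-balance composite.** The *Functional performance* section says that average displacement (AD) in each direction "will be normalized using the length of support leg (LS) of the individual". The composite follows as "CS = AD (ant + postero-medial + postero-lateral)/3 × LS (×100"), with no brackets around the product of 3 and LS.

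The *Secondary outcome* section classes both measures as secondary.

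**The concern.** Both items are rules for turning raw measurements into analysed outcomes, and neither can be followed as printed.

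For the CoP variables, two opposite conventions stand side by side. If the signals are processed by one and the results labelled by the other, a finding on anteroposterior sway is reported as mediolateral sway, and the reverse. Swapped values would look plausible, so the error would be hard to see in the results. The distinction matters for interpretation because dorsiflexion is a sagittal-plane movement.

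For the composite, normal operator precedence gives (sum / 3) × LS × 100. That multiplies by leg length where the preceding sentence asks for normalisation by it. The result would be in cm², would grow with leg length, and could not be read as a percentage of leg length.

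**Working it through.** The protocol gives no worked figure for either rule, so there is nothing to reproduce first.

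**Step 1. Axis statements side by side**

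| Place | Anteroposterior | Mediolateral |
|---|---|---|
| *Postural Control*, direction clause | x (+x anterior) | y (+y right) |
| *Postural Control*, starting position | y (posterior = −Fy) | not stated |
| Variable list after Fig. 4 | Y | X |

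The volunteer's stance does not reconcile them. Facing backwards on the platform is a 180° turn, which sends (x, y) to (−x, −y). It changes signs but does not exchange the axes. If +x is anterior, posterior is −x, not −y. No single coordinate frame satisfies all three rows. The second and third agree, and the first is the outlier.

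**Step 2. How many variables carry an axis label**

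- The list has 7 variables: average speed, two peak speeds, two displacement amplitudes, average XY displacement and ellipse area.
- Labelled by axis: 2 peak speeds + 2 amplitudes = 4.
- Over three reach directions: 4 × 3 = 12 of 7 × 3 = 21.
- The other three variables combine both axes and do not change if the labels are exchanged.

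**Step 3. The composite read two ways**

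The protocol gives no reaches or leg lengths, so all values in cm here are assumptions.

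- Literal: (sum / 3) × LS × 100.
- Bracketed: sum / (3 × LS) × 100.

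| Reaches (cm) | LS (cm) | Literal (cm²) | Bracketed (%) |
|---|---|---|---|
| 60, 95, 90 | 90 | (245/3) × 90 × 100 = 735,000 | 245/270 × 100 = 90.7 |
| 60, 90, 90 | 80 | (240/3) × 80 × 100 = 640,000 | 240/240 × 100 = 100.0 |
| 60, 90, 90 | 100 | (240/3) × 100 × 100 = 800,000 | 240/300 × 100 = 80.0 |

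For the same reaches, the literal score rises with leg length and the bracketed score falls. With reaches at 70% to 100% of leg length and LS from 80 to 100 cm, the literal form runs from 448,000 to 1,000,000 and the bracketed form from 70 to 100.

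The two forms differ by the factor LS²: literal = bracketed × LS². Two participants with the same normalised score and leg lengths of 80 and 100 cm would therefore differ by (100/80)² = 1.5625 on the literal score.

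**The case against.** **The composite is probably only a notation slip.** The sentence before the formula announces normalisation, and the factor of 100 marks a percentage. A stacked fraction flattened onto one line would look exactly like this. A score of 735,000 would also be noticed at once. This stands: the formula is not evidence of a wrong analytical intention. It remains wrong as a written rule. The direction of each participant's change over A0, A1 and A2 survives even under the literal form, because leg length is constant within a person. The weight given to each participant does not, since it scales with LS².

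**The axis outcomes are named anatomically.** The letter is only in parentheses, and two of the three statements agree. A mix-up would apply alike to both groups and all visits, so it would not create a between-group bias, and it could be corrected from stored signals. All of this stands and limits the harm to misreported direction. Two frames might also be in use, one for the body and one for the platform. The protocol does not say so and gives no conversion between them.

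**Stronger readings that the document does not support**

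- A reader might infer that reaches are normalised twice, once when AD is formed and again in the composite. The text measures displacement in centimetres and says that it will be normalised. The formula that follows is naturally where this happens, and nothing says that AD has already been divided by LS.
- A reader might infer from the *Procedures* section, which describes the signal-processing researcher as independent and unaware of earlier steps, that this person will code the article's wording literally. That passage describes independence and blinding. It does not say what instructions the researcher works from.
- A reader might conclude that 12 of 21 CoP outcomes will be mislabelled. That happens only if processing follows the direction clause while reporting follows the variable list.

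**Conclusion.** Both points hold as corrections to derivation rules.

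1. The CoP axis statements contradict each other. Up to 4 of 7 variables, or 12 of 21 across reach directions, could be reported under the wrong direction, on the condition that processing and labelling use different conventions. The document does not settle which convention the platform uses, although two of its three statements take y as anteroposterior.
2. The composite as printed multiplies by leg length, contrary to the stated normalisation. Missing brackets or a flattened fraction is the likeliest cause. The illustrated sizes rest on assumed reaches and leg lengths. That the literal score rises with leg length does not depend on them.

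Severity is minor to moderate. Only secondary outcomes are involved. The primary lunge-test outcome and the sample size are unaffected.

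**What to change.** - In *Postural Control*, state one axis convention, including which way the volunteer faces relative to the platform's axes. The −Fy statement and the variable list agree on y as anteroposterior, so the clause with +x anterior and +y right is the one to re-examine. Check the chosen convention against the platform's own axes, and confirm that the processing script and the variable labels both follow it.
- In *Functional performance*, write CS = [(anterior + posteromedial + posterolateral mean reach in cm) / (3 × LS in cm)] × 100.

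The cost is about two lines of text and a check of the processing script. No new measurements are needed. By the dates under *Trial status*, data collection was expected to end on November 22, 2021. If it has ended, the same check can be applied to the stored signals and reach data before results are reported.

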### Secondary objective

To evaluate the immediate and short-term effect of the associated joint mobilization techniques, Mulligan concept and Maitland method, for the ankle joint, on functional performance and balance*.*

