## Subjects and methods

### Study design

This study is a randomized, controlled, blind clinical trial with two parallel groups (Fig. 1). The study was approved by the Human Rights Ethics Committee under protocol number CAAE: 30660520.1.0000.5152 and registered in the Brazilian Registry of Clinical Trials (ReBEC) (registration number: RBR-93xv9t). Recruitment will begin in September 2020 with a probable end date of November 22, 2021, as a result of the pandemic in the country*.* According to the flowchart (Fig. 1), evaluations will be conducted pre-intervention (A0), post-intervention (A1), and 3–4 days after intervention (A2). Variables to be observed are: Amplitude of Motion of Dorsiflexion of ankle in 20 closed kinetic chain and open kinetic chain, postural balance, and functional performance.

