### Participants and evaluators

Sample calculation was performed using a difference of means and standard deviation, based on closed kinetic chain range of motion, of similar works, being RoM of DF in CKC, primary outcome, performed through the lunge test (LT), and minimum clinically relevant difference of 3.8 degrees [20], with an estimated standard deviation of 4.4°, and considering ANOVA statistical test of repeated measurements. The protocol considered a 0.05 alpha level and an 80% statistical power, being a sample size of 23 volunteers per group. A possible sample loss (15%) was computed, a total of 54 volunteers was considered for randomization.

Eligibility criteria are as follows: men and women between the ages of 18 and 40 will be recruited who have a range of motion (RoM) in closed kinetic chain of less than 40°, verified by lunge test. If the volunteer has bilateral ankle dorsiflexion limitation, the most affected side will be considered for analysis and intervention.

Exclusion criteria are as follows: presenting musculoskeletal injury in the lower limb, rheumatic diseases, cardiovascular diseases, dizziness, vertigo or changes in the vestibular system, neuropathic problems, or any other alteration that could harm the volunteer’s health or compromise performance of tests.

These individuals will be recruited through posters on the campus of the Federal University of Uberlândia (UFU) and by dissemination on social media and local media (TV and radio). So as to increase adherence, especially in the post-intervention evaluations, the volunteers will receive orientation, after final evaluation (A2), as to perform the exercises to maintain or improve ankle RoM.

Research will be developed at the Laboratory of Evaluation in Biomechanics and Neurosciences (LABiN) of the Faculty of Physical Education and Physical Therapy of the Federal University of Uberlândia, Minas Gerais, Brazil.

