### Statistical analysis

The normality test will be performed using the Kolmogorov Smirnov test. If null hypothesis is confirmed, comparison between groups will be performed using parametric tests, however, if null is not confirmed, non-parametric tests will be applied.

For parametric data, the effect of treatment will be evaluated by ANOVA two-way test for repeated measurements, considering a value of *p* ≤ 0.05. Data will be evaluated by intention to treat, through the imputation of the missing data using the *multipleimputation* method. For non-parametric data, the Kruskal-Wallis test will be used. All tests will be calculated using SPSS.

Clinical relevance of results will be confirmed by calculating the effect size (Cohen’s *d*) of significant differences found between assessments. The following effects will be considered: 0.00–0.49, small; 0.50–0.79, medium and above 0.80, large. Analysis of data will be made by intention to treat [29].

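### Balance is assessed on 21 centre-of-pressure variables with no lead variable and one 0.05 rule, and the effect-size step applied to significant results cannot screen out a chance finding

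*Protocol article*

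**What the plan says.** The Secondary objective asks about the immediate and short-term effect of the combined techniques "for the ankle joint, on functional performance and balance". The Secondary outcome section describes postural control as centre-of-pressure (CoP) oscillation during the Y balance test and names no single variable. The Postural Control section lists seven: average speed, two peak speeds, two displacement amplitudes, average displacement and an ellipse area. They are to be calculated "for each test displacement direction", and that section sets three reach directions.

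The Statistical analysis section has one rule for every outcome. It is a two-way repeated-measures ANOVA at p ≤ 0.05, with Kruskal-Wallis where normality is rejected. No order of testing and no adjustment is stated. It then says "Clinical relevance of results will be confirmed by calculating the effect size", and limits the Cohen's d calculation to significant differences between assessments. The grades are small from 0.00, medium from 0.50 and large above 0.80.

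The only clinical threshold in the article is for the lunge test, in Participants and evaluators: "minimum clinically relevant difference of 3.8 degrees". No CoP variable has one.

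**The concern.** Two features act together. First, balance has no single answer: 21 variables can each reach significance, and the article does not say which one decides. Secondly, the relevance step selects on significance and then grades size on a scale with no category for a difference too small to matter. A variable that crossed 0.05 by chance would therefore move on to an effect-size grade offered as evidence of clinical relevance. What is at stake is the secondary conclusion on balance, which the article presents as one of the open questions the trial is meant to address.

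**Working it through.** **Inputs.** The number of CoP variables (7) and of directions (3) come from Postural Control. The threshold of 0.05 and the d bands come from Statistical analysis. Group size is 23 analysed or 27 randomised, from Participants and evaluators. The correlation among the CoP variables is not given, so it is varied from 0 to 0.95 as an assumption.

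**The plan's own figure.** The article states: "The protocol considered a 0.05 alpha level and an 80% statistical power, being a sample size of 23 volunteers per group". The inputs are 3.8 degrees and, in its words, "with an estimated standard deviation of 4.4", so d = 3.8/4.4 = 0.864. A two-sided, two-sample t-test has 79.9% power at 22 per group and 81.7% at 23, so 23 is reproduced. With 15% loss, 46/0.85 = 54.1, against the stated total of 54. This calculation is for the lunge test; the article states no error rate for balance.

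**Count.** 7 × 3 = 21 variables. A two-way ANOVA over A0, A1 and A2 gives one group-by-time test per variable, so 21 treatment tests.

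**Chance of at least one false result, no true effect.** If independent: 1 − 0.95^21 = 0.659.

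For correlated variables the planned ANOVA (2 groups × 3 times, 27 per group) was simulated on normal data with no effects, 8,000 runs per scenario. Each group-by-time F was compared with its 5% critical value.

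| Assumed correlation | At least one false group-by-time result |
|---|---|
| 0 (exact) | 66% |
| 0.3 throughout | 56% |
| 0.5 throughout | 43% |
| 0.7 throughout | 31% |
| 0.8 throughout | 23% |
| 0.9 throughout | 16% |
| 0.95 throughout | 11% |
| 0.7 within a direction, 0.3 between | 43% |
| 0.8 within a direction, 0.5 between | 34% |

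One named variable gives 5%. Holding 5% over all 21 by Bonferroni would need p ≤ 0.05/21 = 0.0024 for each.

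**Can the d step remove a chance result?** The smallest d that a significant result can have is:

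- Simple between-group difference at one time, t(0.975, 2n−2) × √(2/n): 0.59 at n = 23 and 0.55 at n = 27. Both are graded medium.
- Paired change within a group (d on the SD of the change), t(0.975, n−1)/√n: 0.43 at n = 23 and 0.40 at n = 27. Both are graded small.

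Significance thus already forces a d of this size, and the lowest band starts at 0.00. Nothing that enters the step can leave it as not relevant.

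**Does the grade track relevance?** The lunge test allows a check. At SD 4.4, d of 0.546 to 0.594 is 0.546 × 4.4 = 2.4 to 0.594 × 4.4 = 2.6 degrees. That is graded medium, yet it lies below the article's own threshold of 3.8 degrees. The CoP variables have no such threshold, so for them the grade is the only relevance criterion.

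**The case against.** The strongest counter-argument is that this is a condensed article. Choosing a lead variable and handling multiplicity for secondary outcomes is commonly left to an analysis plan, which is not shown. That stands as far as it goes: the missing adjustment alone would not be a finding. The relevance rule, however, is stated here, and it is faulty as written.

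Four stronger readings are tempting, and the article does not support them.

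- *A false balance claim is likely.* For the treatment comparison the chance exceeds 50% only at low correlation. All seven variables come from one CoP signal (speeds go together, amplitudes go with ellipse area), so near-independence is the least plausible case.
- *A1 and A2 double the count to 42 tests, giving 1 − 0.95^42 = 88%.* The planned ANOVA gives one group-by-time test per variable, not separate group comparisons at each visit. Counting time effects as well would also give 42 tests, but a time effect is not a difference between treatments.
- *Every significant result is automatically graded medium or large.* This is true only of a simple group difference at one time. The article applies d to differences between assessments, where a significant paired change can be 0.40 to 0.43, graded small. A between-group difference in change, scaled by the raw SD, can also be small: at an assumed pre-post correlation of 0.7, 0.546 × √0.6 = 0.42, or 0.594 × √0.6 = 0.46.
- *Every significant variable is declared clinically relevant.* The text says relevance is confirmed by calculating d and then grades it. It does not say that a small d counts as relevant. The defect is that the scale cannot reject anything.

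It is also an inference that all 21 are tested separately. The article says they will be calculated and gives one general test rule; it offers no other analysis for them.

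**Conclusion.** The concern holds in a limited form. With 21 CoP variables, no lead variable and one 0.05 rule, the chance of a false treatment finding on balance rises from 5% to somewhere between 11% and 66%. The value depends on correlations that the article does not give. Even at 0.95 the risk is about twice the nominal level. The effect-size step adds no protection, because it is applied only to significant results and has no category for irrelevance.

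This rests on each variable being tested under the general rule, on a normal-theory ANOVA, and on the assumed correlations. It concerns a secondary objective. A reader might infer that the trial's main result is compromised. It is not: the primary outcome is a single named lunge-test variable, and its conclusion is unaffected by this multiplicity.

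**What to change.** Before group labels are released to the analyst:

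1. Name one CoP variable, in one direction or averaged over the three, as the balance outcome. Test it by its group-by-time effect over A0, A1 and A2. Fixing it at A1 alone would drop the short-term half of the Secondary objective.
2. Report the other CoP variables as exploratory between-group differences with 95% confidence intervals. Alternatively, keep their p-values and apply Holm or false-discovery-rate control across the 21.
3. Delete the statement that Cohen's d of significant results confirms clinical relevance. Report d with its confidence interval for all variables, significant or not, as description only.

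Trial status puts the end of data collection in November 2021 and the finalising of the analysis in March 2022. If the data are already unblinded, use the exploratory labelling or the adjustment and state that the choice is post hoc.

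The cost is a change of analysis wording, with no new data and no change in sample size. The downside is fewer individual balance claims.
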